### Covariates

With online questionnaires, we assess demographics; age, gender, nationality, education level and income. We also measure nicotine dependence, which is assessed with the translated Fagerström Test for Nicotine Dependence (FTND [54]). We will control for covariates. First, standard demographics. Second, history of smoking, which is assessed through pack-years [55]. To measure pack-years, we ask in the baseline questionnaire participants how much they smoke and how long they have smoked, which yields an estimate of lifetime smoking exposure. Third, the FTND (see above).

### Effect modifiers

We will explore multiple effect modifiers and gradually build up the models to determine which has the most parsimonious fit. To determine whether regret plays a role in any potential effect, regret proneness is measured via the translated Regret Scale [56]. We use the first question of the Dutch version of the SF-12 as a generic measure of health status [57]. The SF-12 is used to explore the effect of health status on relapse rates. Similar to health status, we will explore the effect of self-reported medication use (yes-no) on relapse rates. If variables moderate the effect, results are also presented separately per group. An overview of all measures is given in Table 1.

**Table 1 Tab1:** Overview of measurements

Measurements	T0 baseline	T1-T2 weeks 1-13	T3 week 26	T4 week 52
Demographics	▲			
Generic health status (SF-12)	▲	▲	▲	▲
Self-efficacy of smoking abstinence (SASEQ)	▲	▲	▲	▲
Motivation to quit (TSRQ)	▲			
Pack-years	▲			
Regret Scale	▲			
Nicotine dependence (FTND)	▲			
Smoking self-reports (text message; RS)	▲	▲	▲	▲
CO-measurements (Smokerlyzer)	▲	▲	▲	▲

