### Sample size calculation

In a meta-analysis, Haff et al. [32] analyzed lottery trials targeted at various health behaviors, with a pooled success percentage of 57.5% in the lottery condition versus 22.6% in the control condition. A sample size calculation for detecting a 0.35 difference between proportions at *p* < .05 and a power (1-*β*) of 90%, indicated a sample size of 40 per condition. With an intra-class correlation coefficient of .05, based on a CRT by Van den Brand and colleagues [21] and an estimated cluster size *m* of 8, a design effect (1 + (*m*-1) x ICC) of 1.35 an effective sample size of 54 per condition was estimated. We aim to recruit a minimum of 64 participants per condition (meaning 8 clusters per condition), allowing 15% participant attrition over time. Based on the power calculation, we aim to assign 16 clusters to receive either a smoking-cessation training or a smoking-cessation training plus the smoke-free lottery.

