### Secondary outcomes

Secondary outcomes for cessation after 13 and 26 weeks will be analyzed similar to the main model. Demographics, nicotine dependence, pack-years and regret proneness will be added as an interaction term with the allocation group to the main model to investigate effect modification. Using survival analyses, we will additionally use the SF-12 measure to explore if perceived health status influences relapse. Analyses are similar for medication use. The SASEQ scores are used to explore if self-efficacy is influenced by treatment (c.f. Van den Brand et al., [58]). We will also explore the determinants of self-efficacy of smoking at baseline with standard regression. Explorations for motivation to quit are similar. To further explore if regret proneness influences treatment effects, we will also perform a regression analysis within the lottery-arm, with abstinence at 13, 26 and 52 weeks as dependent variable and regret proneness, as well as covariates from the main model as independent variable.

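### Subgroup results for eight candidate effect modifiers are selected by model fit and displayed when moderation is observed, with no criterion, so a chance subgroup display is fairly likely

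*Protocol article*

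**What the plan says.** Three places in the protocol article bear on this point.

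- **Effect modifiers (Data collection).** The approach is "We will explore multiple effect modifiers and gradually build up the models to determine which has the most parsimonious fit", followed by the display rule "If variables moderate the effect, results are also presented separately per group". Neither sentence names a fit criterion, a significance level or a definition of moderation.
- **Secondary outcomes (Statistical methods).** The candidates are named: "Demographics, nicotine dependence, pack-years and regret proneness will be added as an interaction term with the allocation group to the main model".
- **Covariates (Data collection).** The demographics are listed: "we assess demographics; age, gender, nationality, education level and income". These five plus the other three make eight.

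Health status and medication use also stand under the Effect modifiers heading, but their stated analyses differ. For the first, "we will additionally use the SF-12 measure to explore if perceived health status influences relapse"; for the second, "we will explore the effect of self-reported medication use (yes-no) on relapse rates". Both ask what influences relapse, and no interaction with allocation is stated for either.

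**The concern.** Choosing interactions by fit, and showing separate effects where moderation appears, makes the observed result decide which subgroup contrasts the reader sees. With several candidates and no true moderation, some variable will often look like a modifier by chance. The contrast then displayed is also exaggerated, because it was picked for being large.

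The practical risk is a statement such as the lottery working at one education or income level and not at another. The abstract's discussion mentions effectiveness across socioeconomic groups as part of the background interest, so a chance finding there could be taken up by readers.

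This differs from a detail left to a statistical analysis plan. The article states the selection and display rules, and an analysis plan that followed them would inherit the selection.

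**Working it through.** **1. Planned size (Sample size calculation).** The rates are given "with a pooled success percentage of 57.5% in the lottery condition versus 22.6% in the control condition". With two-sided 0.05, 90% power, pooled variance and no continuity correction, n = 40 per condition. The design effect is 1 + (8 − 1) × 0.05 = 1.35, and 40 × 1.35 = 54. Allowing for 15% attrition, 54 / 0.85 = 63.5, so 64 per condition. This reproduces the protocol's 40, 54 and 64. The total is 2 × 64 = 128. The article states no error rate for the effect-modifier analyses, so there is no figure of that kind to reproduce.

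**2. Number of candidates.** 5 demographics + nicotine dependence + pack-years + regret proneness = 8.

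**3. Chance of at least one false modifier, no true moderation.** For k independent tests each judged at level a, the chance is 1 − (1 − a)^k. The level a is an assumption throughout.

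| k | a | Chance |
|---|---|---|
| 8 | 0.05 | 1 − 0.95^8 = 33.7% |
| 8 | 0.01 | 1 − 0.99^8 = 7.7% |
| 8 | 0.10 | 1 − 0.90^8 = 57.0% |
| 4 (demographics counted once) | 0.05 | 1 − 0.95^4 = 18.5% |
| 10 (health status and medication use added as modifiers) | 0.05 | 1 − 0.95^10 = 40.1% |

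**4. Correlated tests.** Simulating eight equally correlated two-sided z-tests at 0.05 gives:

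| Correlation | 0.1 | 0.2 | 0.3 | 0.5 | 0.7 |
|---|---|---|---|---|---|
| Chance | 33.1% | 32.0% | 30.0% | 25.0% | 19.1% |

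**5. Selection by fit.** The article speaks of fit rather than p-values, so fit criteria were also tried. In 2,000 simulated trials of 128 participants at the planned rates with no moderation, each of eight continuous modifiers was given a main effect and then an interaction with arm. The share of trials in which at least one interaction passed was:

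| Entry rule for the interaction | Independent modifiers | Modifiers correlated 0.2 |
|---|---|---|
| Likelihood-ratio p < 0.05 | 36% | 35% |
| AIC improves (chi-square > 2) | 77% | 74% |
| BIC improves (chi-square > ln 128 = 4.85) | 21% | 21% |

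This simulation used ordinary logistic regression without clustering and took the interactions one at a time. It approximates the first step of a forward build-up, where the best single interaction either enters or does not. It does not reproduce the planned random-intercept model.

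**The case against.** The strongest reply is that this is openly exploratory work in a condensed article. Thresholds and multiplicity rules for exploratory subgroups usually sit in an analysis plan, which is not shown. Much of that reply stands, and it rules out several stronger readings that a reader might infer.

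- **That eight interactions are screened one by one at full alpha.** The article describes gradual model building. Its only significance level belongs to the main comparison: "A sample size calculation for detecting a 0.35 difference between proportions at" p < .05. A one-in-three error rate is therefore an illustration and not a property of the trial.
- **That null interactions go unreported.** The display rule concerns results shown in addition. It does not say that other interaction tests are suppressed.
- **That the family is open-ended.** Statistical methods names the interaction set, and Covariates lists the demographics.
- **That the main treatment estimate is distorted.** The Primary outcome and Covariates sections under Statistical methods define a model with allocation, adjusters and random intercepts. Interactions appear only under Secondary outcomes.
- **That a confirmatory claim about regret is planned.** The language is exploratory, and Strengths and limitations concedes that the design cannot separate the psychological mechanisms.
- **That a multiplicity correction is required.** For exploratory interactions it is a matter of judgement, and it would cost power.

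The reply does not remove the written rule itself. Calling the work exploratory does not prevent the selection that follows when fit and observed moderation decide what is displayed.

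**Conclusion.** The point holds as a correctable weakness in a secondary analysis. Eight allocation interactions, selection by fit and a display triggered by the result are all stated in the article, without a criterion for moderation. In a trial of about 128 participants this makes a chance subgroup display fairly likely.

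The central illustration is 34%, falling to 25% at a test correlation of 0.5. It assumes eight candidates, no true moderation and an unstated 0.05 threshold. Across other plausible criteria the figure runs from about 8% (each test at 0.01, independent) to about 77% (AIC, independent modifiers). The range is wide because the article leaves the criterion open, so no single value should be quoted as the trial's error rate. The primary test and its error rate are untouched.

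**What to change.** In the Effect modifiers section, replace the sentence on parsimony-based model building and the sentence on separate presentation with text to this effect:

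*Interactions of allocation with age, gender, nationality, education level, income, nicotine dependence, pack-years and regret proneness will each be estimated, and all eight estimates will be reported with confidence intervals whatever the result. Regret proneness by allocation at week 52 is the one mechanism-linked modifier; the other seven are hypothesis-generating.*

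This removes the selection at its source, so no threshold for moderation is needed. The cost is wording only, with no new data and no extra participants. The downside is that the other seven modifiers can no longer support a stand-alone subgroup claim. A Holm adjustment across the family is optional and is not part of this change.

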### Statistical methods

Descriptive analyses (mean, standard deviation, frequencies and percentages) on nationality, age, sex, Fagerström score, education, income and pack-years are used to display the baseline composition of both groups.

### Primary outcome

The analysis of the primary outcome examines the difference in continuous smoking abstinence between intervention group and control group 52 weeks after the quit date. After 52 weeks, a multi-level logistic regression analysis will be performed. The proportion of verified continuous abstinent participants is the dependent variable. The allocation group is the independent variable. Participants are the primary unit of inference and are clustered within organizations. Random intercepts are added at the organization level to account for clustering of observations within organizations. The multi-level model estimates the treatment effects after 52 weeks, while accounting for the clustered data pattern.

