### Study design

We propose a two-arm, parallel group, cluster-randomized trial running for 52 weeks in 16 organizations (clusters) across the Netherlands. We aim to assign organizations to receive either a smoking-cessation training (8 companies) or a smoking-cessation training plus the smoke-free lottery (8 companies). Participants in both arms participate in an identical 8-week smoking cessation group training at the workplace. Participants in the lottery condition will additionally participate in 13 weekly lotteries starting from the prespecified joint quit date, complemented with a long-term lottery after 26 weeks. A schematic representation of the trial is presented in Fig. 1. The trial protocol and materials were reviewed and approved by the Radboud University Ethical Review Board (ECSW-2019-114). The study is registered in the Dutch Trial Register (NTR NL8463) and lottery drawings are performed by an independent notary.

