### Strengths and limitations

The current trial is subject to several limitations. First, randomizing clusters and not participants increases the probability that intracluster effects influence results. That is, observations within clusters are correlated. As a result, the required sample size is higher than would be the case with randomization at the participant level and clustering must be accounted for in the statistical models. We aim to account for clustering in the multilevel model by allowing random intercepts.

Randomization at the cluster level has the practical benefit that employers can communicate clearly what the program entails to the entire company at once. A company’s limited communication-resources (mostly time) and competing internal messaging (e.g., newsletters) mean that raising employees’ attention for participation in scientific studies requires highly digestible homogeneous information. Our experience is that one key message, communicated to a single cluster improves this.

A methodological benefit of cluster randomization is that it can avoid treatment contamination of participants within companies or groups [67]. Contamination occurs when participants in the control arm receive active intervention influences from the intervention arm. This makes the control arm more similar to the intervention arm, reduces their intended randomized contrast and hinders the possibly for causal inference [67].

In our trial, randomization at the individual level would have resulted in participants in one training group receiving different treatments. In that case, cessation group members allocated to the control arm could be influenced positively by their peers receiving incentives or negatively as they are not eligible for a prize, while their peers are. Likewise, participants in the intervention arm interacting with nearby participants in the control arm might share their prizes with those not allocated to the lotteries. Taken together, cluster randomization was reasoned to be the best design for testing a group-based intervention in this context.

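### With 16 organizations, a random intercept alone does not hold the primary test at 5% under the usual large-sample tests; tie the test to a t distribution with between-cluster degrees of freedom

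*Protocol article*

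**What the plan says.** The Study design section describes a "cluster-randomized trial running for 52 weeks in 16 organizations (clusters) across the Netherlands", 8 per arm. Under Statistical methods, Primary outcome, the article states "After 52 weeks, a multi-level logistic regression analysis will be performed", with allocation as the independent variable and a random intercept per organization. The Covariates paragraph that follows adds Fagerström score, education, income, age and gender, and leaves online versus in-person training to be explored as a further covariate. Strengths and limitations returns to the subject: "We aim to account for clustering in the multilevel model by allowing random intercepts". The secondary cessation outcomes at 13 and 26 weeks are to be analysed in a similar way.

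None of these places names a Wald, likelihood-ratio or t test, a degrees-of-freedom rule, or any allowance for the small number of clusters. The Sample size calculation section multiplies a two-proportion sample size by a design effect and makes no separate allowance for few clusters.

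**The concern.** A random intercept models the correlation between colleagues. It does not by itself allow for the fact that the between-organization variance is estimated from only 16 units. Most software reads the treatment coefficient of such a model against a normal or chi-square distribution by default. With 14 between-cluster degrees of freedom, those reference distributions are too tight.

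The variance is also often estimated as exactly zero when clusters are small and the ICC is low. The fit is then ordinary logistic regression, with no widening for clustering.

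At stake is the error rate of the single primary test, and the departure is in the direction of a false positive.

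**Working it through.** **Inputs from the documents.** Sample size calculation: "with a pooled success percentage of 57.5% in the lottery condition versus 22.6% in the control condition"; "indicated a sample size of 40 per condition"; "With an intra-class correlation coefficient of .05"; "an estimated cluster size *m* of 8, a design effect (1 + (*m*-1) x ICC) of 1.35"; 5% significance, 90% power, 15% attrition, 64 participants and 8 clusters per arm. Study design: 16 clusters. The carbon monoxide measurement section counts non-responders as smokers.

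**Step 1. Reproduce the plan's figure.** Two-sided normal formula with pooled variance under the null: n = [1.960 x sqrt(2 x 0.4005 x 0.5995) + 1.282 x sqrt(0.575 x 0.425 + 0.226 x 0.774)]² / 0.349² = [1.960 x 0.6930 + 1.282 x 0.6475]² / 0.1218 = 39.3, so 40 per arm. Then 40 x 1.35 = 54, and 54 / 0.85 = 63.5, so 64. The figure reproduces exactly, as a normal-approximation figure.

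**Step 2. Rough size of the effect on the test.** The 5% two-sided critical value of t on 14 df is 2.145, against 1.960 for z. A statistic that follows t on 14 df but is judged at 1.960 rejects 7.0% of the time, so the nominal 95% interval covers about 93.0%. The t interval is 2.145 / 1.960 = 1.09 times as wide.

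**Step 3. Simulate the planned analysis with no treatment effect.** 8 + 8 clusters of mean size 8 (equal, or varying from 2 to 16), beta-binomial outcomes, null rates of 22.6% and 40%, random-intercept logistic model fitted by quadrature, 4,000 trials per setting (Monte Carlo standard error about 0.4 points).

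| ICC | Wald z | Likelihood ratio | Wald on t(14) | Cluster-level t-test |
|---|---|---|---|---|
| .05 (plan) | 6.4-7.0% | 6.0-6.4% | 4.5-4.7% | 5.2-5.3% |
| .10 (assumed) | 7.3-8.1% | 6.7-7.1% | 5.1-5.6% | 5.0-5.4% |

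At ICC 0 (assumed) Wald z gives 4.3-5.1%, so there is no inflation. With the five planned covariates added as pure noise at ICC .05 (3,000 trials), Wald z gives 6.3-6.5%, likelihood ratio 6.1-6.3% and t(14) 4.5-4.6%. Separate simulations of the same design at ICC .05 gave 6.2-6.7% for Wald z and 3.9-4.7% for t(14). One at ICC .10 gave 6.9% for Wald z. The variance was estimated as zero in 33-38% of the null trials at ICC .05.

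**Step 4. Power if t(14) is used.** Effective n = 64 / 1.35 = 47.4 per arm. The noncentrality is 0.349 x sqrt(47.4) / 0.6475 = 3.71, and a noncentral t on 14 df gives 93.1%. Simulated power of the model on t(14) at 64 per arm is 92% with equal clusters and 90% with varying sizes. At 54 per arm the noncentral t gives 88.6%.

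**Step 5. Cost in power at 64 per arm.** Against the plan's pooled z formula: 94.7 - 93.1 = about 1.5 points. That mixes a pooled and an unpooled variance. With the unpooled variance on both sides it is 96.0 - 93.1 = 2.9 points. In simulation it is 94.6 - 92.0 = 2.6 points (equal sizes) and 92.9 - 89.9 = 3.0 points (varying sizes).

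**The case against.** The strongest reply is that the article names no test at all. It is a condensed account, its statistical analysis plan is not shown, and a reference distribution or degrees-of-freedom correction is the kind of detail such a plan holds. A random intercept at the level of randomization is an accepted analysis. This stands to the extent that the article cannot be said to have chosen a wrong test, and the absence of a named test is not the point here. What remains is that the article presents the random intercept as its remedy for clustering, and with 16 clusters that remedy, under either usual large-sample test, does not hold 5%.

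Two stronger readings are tempting and are not supported.

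- A reader might infer that the trial is underpowered because the power figure rests on a normal approximation. That would need about 54 analysed per arm (88.6% under t). The article counts non-responders as smokers and analyses by intention to treat, so the 64 recruited stay in the denominator.
- A reader might infer that clustering goes uncorrected, unnoticed, in about a third of trials. Those zero-variance fits are already inside the 6-7% overall error and are not a further harm. A zero variance estimate also shows in the model output.

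It is also fair to say that the excess is only 1-2 points at the plan's ICC.

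**Conclusion.** The concern holds as a modest risk in the stated model, conditional on how the model is read. With a Wald z or likelihood-ratio test, at the plan's ICC of .05 and about 8 per cluster, the primary test rejects in about 6-7% of null trials and the 95% interval is slightly too narrow. On t with 14 df the error is about 4-5%.

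This rests on an 8 + 8 split, which the biased urn may not deliver exactly, on beta-binomial clustering, and on null abstinence rates of 22.6% and 40%. The ICC achieved in the trial is unknown. A value nearer .10 would raise the Wald z error to about 7-8%, and a value near 0 would remove the excess. The sample size and the 90% power claim are not shown to be wrong.

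**What to change.** Keep the random-intercept logistic model. Before the outcome data are analysed, state that the treatment effect is tested, and its confidence interval formed, on a t distribution with between-cluster degrees of freedom: clusters minus 2, which is 14 at 8 + 8. Each organization-level covariate takes one more, so 13 if online versus in-person training varies by organization and enters the model. Apply the same rule to the 13- and 26-week abstinence models.

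Prespecify one sensitivity analysis: a cluster-level t-test, or a permutation test whose re-allocations follow the biased-urn scheme. It should not replace the primary test when the variance happens to be estimated at zero, because that would let the data choose the primary analysis. A simple cluster-level t-test does not carry the five individual covariates and estimates a different effect measure, which is a further reason to keep it secondary.

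The cost is a few sentences, an interval about 9% wider on the log-odds scale, and about 1.5-3 points of power (nearer 3 on a like-for-like comparison). If the true ICC is close to zero, the t reference is somewhat conservative: about 3% error at ICC 0 and a 40% null rate. A permutation test that follows the urn takes some programming. No added clusters and no restated power are needed.
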